## Abstract

**Abstract:**

**Introduction:**

The impact of preoperative weight loss and body composition changes on surgical and patient-reported outcomes remains unclear in gastrointestinal cancer patients. Prehabilitation programmes integrating exercise, nutrition and psychological support can improve surgical readiness and recovery but the role of body mass and composition changes within such services is not well understood. This study aims to investigate the associations between preoperative changes in body mass and composition and surgical, physical fitness, nutritional and quality of life outcomes among people with obesity undergoing surgery for upper gastrointestinal or colorectal cancer within the context of a cancer prehabilitation service (Active Together).

**Methods and analysis:**

This prospective observational study will recruit 100 adults (≥18 years; body mass index ≥30 kg/m²) scheduled for curative upper gastrointestinal or colorectal cancer surgery and enrolled in the Active Together prehabilitation service. Participants will attend two study visits: one as soon as possible after diagnosis and one within 2 weeks before surgery. Participants will undergo body mass, composition and size measurements and complete questionnaires on their nutritional status and quality of life. Routinely collected surgical outcomes (complications, operative approach and duration, length of hospital stay, readmissions, 1-year survival) and Active Together assessment data (physical fitness, psychological well-being, nutritional status) will also be collected. Correlation analyses and regression models will be used to explore the associations between preoperative changes in body mass and composition and surgical, physical fitness, nutritional status and quality of life outcomes.

**Ethics and dissemination:**

Ethical approval has been obtained from the Health Research Authority (Integrated Research Application System project ID 361634; Research Ethics Comittee reference 26/YH/0019). Written informed consent will be obtained from all participants. Data will be processed in accordance with General Data Protection Regulations and the Data Protection Act 2018. Findings will be disseminated via peer-reviewed publications, conference presentations and patient and public involvement activities.

STRENGTHS AND LIMITATIONS OF THIS STUDYThe observational nature of the study provides an ecologically valid insight into patient outcomes in an evidence-based cancer prehabilitation service.Longitudinal assessment of body mass and composition, surgical outcomes, physical fitness, nutritional status and quality of life allow investigation of the relationships between the changes in each metric across the perioperative period.The observational nature of the study precludes the ability to draw causal inferences.The potential heterogeneity of participant characteristics and treatment pathway may confound the associations reported; however, these will be accounted for statistically where possible.

## Introduction

 Gastrointestinal (GI) cancers are a leading cause of global morbidity and mortality^1 2^ and induce significant costs to health services.^3^ Surgical intervention (eg, resection) is a primary treatment for GI cancers.^4^ However, surgery carries the risk of complications, risks which are increased for individuals with obesity.^5 6^ Consequently, patients with obesity are advised to lose weight prior to surgery.^7^ Previous research has shown that weight loss is feasible in a pre-surgery context for cancer patients^8^ and does not lead to increases in length of stay or postoperative complications.^9 10^ Indeed, a recent randomised controlled trial feasibility study investigating intentional pre-surgery weight loss in colorectal cancer patients reported no difference in complications between the weight loss and usual care group, and that those who lost more than 3.2% of their body weight had a 50% reduction in surgical complications.^11^

However, although weight loss may make the surgical procedure easier for surgeons to perform and/or reduce the risk of surgical complications, the effects of weight loss must be viewed within the context of the whole cancer patient journey. Indeed, greater preoperative weight loss is associated with worse long-term outcomes such as mortality and disease recurrence in upper GI and colorectal patients.^1012^,^14^ A possible explanation is that weight loss prior to surgery, particularly rapid weight loss, may result in the reduction of not only fat mass but also muscle mass, which is associated with increased mortality^15^ and is linked to metabolic disease.^16^ Additionally, low muscle mass has been associated with post-operative complications in cancer patients undergoing gastric surgery.^17^ Estimates suggest that one in two people with cancer will experience cachexia,^18 19^ which causes approximately 20–30% of all deaths in cancer patients.^20 21^ Consequently, interventions with the potential to exacerbate cachexia require thorough evaluation prior to adoption.

Therefore, presurgery weight loss offers potential benefits and drawbacks that may be dependent on the actual body composition changes that occur; lower fat mass might be beneficial for reducing surgical complications, but reduced muscle mass is likely detrimental for overall morbidity and mortality. Until the effects of preoperative weight loss are better understood, it may not be appropriate to encourage patients to lose weight.^22^ A greater understanding of these factors would help to generate evidence-based recommendations for cancer patients providing much needed guidance for dietitians and specialist exercise professionals working with people affected by cancer.

Current recommendations advocate for prehabilitation programmes for cancer patients,^23^ which is the use of targeted interventions between the time of diagnosis and acute treatment to promote health and reduce the risk of future impairments.^24^ Prehabilitation interventions including exercise, nutrition and psychological support (either alone or in combination) have been shown to improve patient outcomes such as surgical complications, length of hospital stay and quality of life compared with usual care, and thus should be considered in standard care.^25^ Indeed, the National Cancer Plan for England acknowledges the importance of cancer prehabilitation and sets out the ambition to deliver a national ‘digital first’ prehabilitation offer by 2028.^26^ Therefore, investigating the effects of preoperative weight loss within a prehabilitation service will provide valuable information that could benefit individuals within this type of service.

Active Together is a multimodal prehabilitation and rehabilitation service in South Yorkshire, UK, which provides support to cancer patients to prepare for and recover from treatment.^27^ The service, which was co-designed by cancer patients, clinicians, professionals and academics, provides exercise, nutrition and psychological support to patients throughout the cancer care journey, spanning from prehabilitation before and during treatment to restorative and supportive rehabilitation after treatment.^28^ Patients are referred to the service after diagnosis where they undergo assessments to ascertain their physical, nutritional and psychological status, before receiving person-centred support underpinned by behaviour change techniques.^28^

The measures of physical function, dietetic need and psychological well-being that are routinely collected by Active Together are useful for understanding patient experience and outcomes throughout their cancer journey. However, the impact of preoperative changes in body weight and composition on these measures is currently unknown. Therefore, combining the primary data from this study with the data collected by the Active Together service will provide a rich and novel insight into patient outcomes in response to surgery within the context of body mass and composition changes.

The aim of this study is therefore to investigate the associations between preoperative body mass and composition changes and surgical outcomes, physical fitness, nutritional status and quality of life in patients living with GI cancer and obesity within a (p)rehabilitation context.

## Methods and analysis

### Study design

This is a prospective observational study to assess changes in patient body weight and composition during the preoperative phase of GI cancer treatment and the associations these have with surgical outcomes, physical fitness, nutritional status and quality of life. Recruitment and data collection for this study will take place between April 2026 and February 2027. Participants will complete two data collection sessions for this study: once as soon as possible after diagnosis and once within the 2 weeks prior to surgery. The time between the first and second visits will vary depending on tumour location, wait times for surgery and length of neo-adjuvant treatments (if applicable).

As well as these two data collection sessions, participants will continue to receive their usual care from the Active Together (p)rehabilitation service, which includes assessments at pre-defined time points throughout their cancer care journey. The data collected from these assessments will be used for this study, as well as surgical data that will be collected from the surgical team and hospital records. Figure 1 provides an overview of the timing and type of data collected from each source, and the Procedures section details the outcome measures collected from each source.

**Figure 1 F1:**
[figure not shown]
Schematic of data collection in relation to study-specific visits, surgery, and the Active Together assessment pathway. Data will be collected by the Active Together service at baseline, pretreatment and post-treatment, and at 90 days post treatment. Active Together define treatment to include additional forms of acute treatment, for example chemo or radiotherapy, and so pretreatment and post-treatment assessments may occur at varying intervals from surgery. Study-specific data will be collected twice: once as soon as possible after diagnosis, and once within the 2 weeks prior to surgery. Due to differences in treatment pathways and surgery waiting times, the duration between visit 1 and visit 2 will vary between participants, as well as the duration between Active Together assessments. Surgical data will be collected from the surgical team after patient discharge. The study specific, surgical and Active Together outcomes are outlined in the Procedures section.

### Participants

This study will recruit participants from the South Yorkshire Active Together (p)rehabilitation service who are 18 years or older, have a body mass index (BMI) of ≥30 kg/m^2^ and are candidates for curative upper GI or colorectal surgery as part of their cancer treatment. Exclusion criteria are pregnancy and those who are unable to complete the study procedures or provide informed consent (lack capacity). Prospective participants will be screened for eligibility by checking the patient’s age, cancer type, treatment plan and BMI. All individuals who meet the eligibility criteria will be provided information about the study by clinicians in routine Active Together sessions and their details passed to the research team with the prospective participant’s consent. Alternatively, potential participants will be contacted directly by a member of their clinical team. Participants will be reimbursed for their travel and will be given a £25 voucher on completion of the second study visit.

### Procedures

#### Primary data

Participants will be required to attend the Advanced Wellbeing Research Centre (AWRC) at Sheffield Hallam University on two separate occasions. The first visit will take place as soon as possible after diagnosis, during which participants will complete two questionnaires and four physical assessments. On arriving at the AWRC, participants will be greeted by a member of the research team and taken to the morphology lab where they will be seated in a neutral space with no sight of the equipment. The researcher will explain the study again and provide an opportunity to ask any questions before the participant provides their informed consent to participate.

Participants will then be asked to complete the following questionnaires: the EuroQol 5-Dimensions 5-Levels (EQ-5D-5L) to measure quality of life^29^ and the Patient Generated Subjective Global Assessment Short Form (PG-SGA-SF) to measure nutritional status.^30 31^ Next, participants will be asked to void their bladder, change into form-fitting, non-compressive clothing, and remove all jewellery to complete the four physical assessments: stature (Seca 264, Seca, Germany), body mass and body composition (proportions of fat and fat-free mass) using a BOD POD (Cosmed, Italy) and body size and shape (including waist, upper arm, and calf circumference) using the Size Stream SS20 3D body scanner (Size Stream, NC, USA). The second visit will take place within the 2 weeks prior to the participant having surgery, and the data collection for this visit will be the same as visit one, with the addition of another questionnaire to gather information on participants’ weight loss intentions, strategies and advice received; see online supplemental material 1.

For the body composition and size measurements, participants will wear form-fitting, non-compressive clothing and a swim cap. Additionally, participants will be asked to refrain from eating or exercising within the 2 hours prior to the visit and to arrive in a normal state of hydration (ie, not drinking any more or less than they usually do). If a medical condition precludes a participant from fasting, they will be instructed to record what they eat before the session and to replicate this for the second session. The BOD POD estimates body composition using air displacement plethysmography, for which the procedure requires participants to be weighed on a set of calibrated scales and then sit inside the pod for approximately 3 min (two or three 45-second measurements). If participants are unwilling or unable to use the BOD POD, they will instead have their body composition measured using a set of bioelectrical impedance scales (TANITA MC-780MA-N S, TANITA Europe, Netherlands). The Size Stream SS20 procedures require participants to stand still inside the device for approximately 20 s (a single 6-second measurement).

For participants that are eligible and wish to volunteer to take part in the study but express that they are unable to attend the AWRC site, a member of the research team will conduct the two data collection sessions where the participant attends Active Together sessions. These sessions will not include BOD POD and Size Stream measurements and instead only include body mass and composition measurement performed using the bioelectrical impedance scales and questionnaires. These participants will be included in the study to maximise recruitment and the amount of data collected, as well as attenuating the bias of the data towards participants that are more mobile/have access to transport/live closer to the AWRC.

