**Figure 2 F2:**
[figure not shown]
Directed acyclic graph for investigating the effect of body composition changes on surgical outcomes. Baseline and preoperative well-being include nutritional status, psychological well-being and physical fitness.

Pearson (or Spearman, depending on the distribution of the data) correlation coefficients will be calculated to explore associations between outcome measures (eg, body weight, size and shape, body composition, body mass change, PG-SGA-SF, EQ-5D-5L, etc) and clinical outcomes (eg, surgical complications, length of stay, number of emergency readmissions and length of operating time). P values <0.05 will be considered statistically significant. Linear and multivariate regression models will then be used to investigate the strength of associations between preoperative changes in patient body measures (eg, body weight and composition), self-reported outcomes (ie, questionnaire data) and clinical outcomes. Additionally, exploratory analyses comparing outcomes between groups of participants (eg, those that lose weight vs those that do not) will be completed, with groups created using thresholds used in the previous literature^10^ and/or data-driven approaches such as a median split^11^ or optimal cut-point determination^32^.

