Separate linear regression models will be created to investigate the amount of variation in self-reported and clinical outcomes which are explained by preoperative changes in patient body measures. Then, multivariate regression models will be created which combine patient outcome measures that contribute significantly to the estimation of clinical outcomes. Ordinal logistic regression models will also be used to explore the relationship between patient outcome measures and ordinal clinical outcome variables, such as surgical complications (Clavien-Dindo classification) and the surgical approach used. Where the distribution of data indicates it would be appropriate (ie, for non-linear relationships between predictor and outcome variables), other regression approaches such as restricted cubic splines or generalised additive models will be used. Regression analyses are appropriate as this is exploratory research, and this approach allows the observation of relationships between all variables. The regression models will all be adjusted for the variability in time between the assessment points, tumour group and pretreatment therapies where these are shown to reduce residual variance and not introduce collinearity to the model. Any outliers will be investigated to ensure that they are legitimate observations; only implausible data will be removed.

Multiple regression models will be assessed for multicollinearity between input variables using variance inflation factor and tolerance collinearity statistics and for independence of errors using the Durbin-Watson test statistic. If the largest variance inflation factor value is >10, or tolerance values are below 0.2 this could indicate potential issues in the model associated with multicollinearity. Also, if Durbin-Watson values differed significantly from two this would suggest dependence of errors between input variables in the model. Additionally, regression assumptions (eg, homoscedasticity, normally distributed errors) will be checked via diagnostic plots, and transformations of variables will be used if assumptions are not met.

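### The rule of screening body measures one at a time, with composition described only as proportions, does not reliably separate fat loss from fat-free loss; one prespecified joint model in kilograms would

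*Protocol article*

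**What the plan says.** All references are to the protocol article.

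- **Measurement (Procedures, Primary data).** Both visits record "body mass and body composition (proportions of fat and fat-free mass) using a BOD POD (Cosmed, Italy"). Weighing is part of the same session: "the procedure requires participants to be weighed on a set of calibrated scales". Participants who do not use the BOD POD have mass and composition taken on impedance scales.
- **Rationale (Introduction).** The tissues are expected to work against each other: "lower fat mass might be beneficial for reducing surgical complications, but reduced muscle mass is likely detrimental for overall morbidity and mortality".
- **Aim (end of Introduction).** It is wider than that contrast: to "investigate the associations between preoperative body mass and composition changes and surgical outcomes, physical fitness, nutritional status and quality of life".
- **Exposures (Statistics and analysis).** They are named only by example: "preoperative changes in patient body measures (eg, body weight and composition"). No unit or scale is given.
- **Model building (same section).** First, "Separate linear regression models will be created to investigate the amount of variation in self-reported and clinical outcomes" explained by these changes. Then, "multivariate regression models will be created which combine patient outcome measures that contribute significantly to the estimation of clinical outcomes".
- **Collinearity check (same section).** Trouble is flagged thus: "If the largest variance inflation factor value is >10, or tolerance values are below 0.2".

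**The concern.** The proportions of fat and fat-free mass add to 100%, so their changes are one variable with opposite signs. Body mass is the sum of the two tissues. A one-at-a-time model on either measure therefore reports a blend. Body mass change adds the tissues together, so opposing effects can cancel. Percent-fat change moves when either tissue moves and stays still when both fall in proportion.

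Using kilograms does not by itself solve this, because of the selection rule. When two predictors are positively correlated and their effects oppose, each hides the other in a single-predictor model. Combining only the significant ones can then discard one or both. That is the configuration the Introduction puts forward. At stake is whether the study can say, for dietitians and exercise professionals, which tissue loss goes with which outcome.

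**Working it through.** **Plan's own figure.** The article gives no figure on this point. Its sample size does reproduce: for f² = 0.15, six predictors and two-sided 5%, the noncentral F test with 6 and 91 degrees of freedom has power 0.804 at N = 98 (0.813 at N = 100). The simulations below use N = 100.

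**1. What the recorded variables contain.** Let M be body mass and p the fat proportion.
- Fat = pM and fat-free = (1 − p)M, so both kilogram changes can be recovered exactly.
- Δ(1 − p) = −Δp. With an intercept, the two proportion changes give rank 2 of 3.
- ΔM = Δfat + Δfat-free. With an intercept, all three kilogram changes give rank 3 of 4.
- Δfat with Δfat-free, or ΔM with Δp, is full rank.

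**2. What percent fat alone can show.**
- 100 kg at 42% fat, 5 kg lost in proportion: fat 42 to 39.9 kg, fat-free 58 to 55.1 kg, and 39.9/95 = 42.0%. No change is seen.
- 105 kg at 45% fat (47.25 kg). Losing 5 kg of fat gives 42.25/100 = 42.25%. Gaining 6.83 kg of fat-free mass gives 47.25/111.83 = 42.25%. These are different events with the same Δp.

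**3. Why the screen fails with opposing effects.** Put both changes in SD units with correlation ρ and effects +β (fat) and −β (fat-free) on an adverse outcome. The single-predictor slope for fat is β − ρβ = β(1 − ρ), and likewise in size for fat-free. With β = 0.35 it shrinks from 0.35 to 0.245, 0.175 and 0.105 at ρ = 0, 0.3, 0.5 and 0.7. The joint model still estimates 0.35 for each.

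**4. Simulation.** Every input is an assumption; the documents give none. N = 100, SD of change 3 kg fat and 2 kg fat-free, effects 0.35 per SD, residual SD 1, two-sided 5%, no covariates.

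| Correlation of the two changes | 0 | 0.3 | 0.5 | 0.7 |
|---|---|---|---|---|
| Both kg changes pass the one-at-a-time screen | 80% | 34% | 7% | 0% |
| Both significant in one joint model | 84% | 82% | 73% | 57% |

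In the same scenario:
- Body mass change is significant in about 14% and 8% of runs at correlations 0 and 0.3, and in 6% or fewer beyond that.
- Percent-fat change is significant in about 99% at correlation 0, 94% at 0.3 and 48% at 0.7.

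**5. Sensitivity to the assumed effects.** With smaller slopes (0.10 per kg fat and −0.15 per kg fat-free, that is 0.10 × 3 = 0.15 × 2 = 0.30 per SD):

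| Correlation | 0 | 0.3 | 0.5 | 0.7 | 0.9 |
|---|---|---|---|---|---|
| Both pass the screen | 64% | 21% | 3% | 0.3% | 2% |
| Both significant jointly | 68% | 66% | 58% | 44% | 19% |
| Variance inflation factor, joint model | 1.0 | 1.1 | 1.4 | 2.0 | 5.5 |

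**6. If only fat-free loss matters** (0.35 per SD, correlation 0.3): percent-fat change has about 10% to 12% power, body mass change about 66% to 71%, and the fat-free term in the joint model about 90%.

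**The case against.** The strongest reply is that nothing is lost. Mass and proportion are both recorded, so the tissues can be separated. The bracketed description sits in Procedures and says what the device measures, not which exposure is regressed. A journal article may leave scale and parameterisation to a fuller plan. The work is declared exploratory, and its aim covers more than fat against lean.

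Much of this stands, and it rules out several stronger readings that a reader might infer.

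- *That the study cannot separate fat from lean loss.* It can, by the algebra in step 1.
- *That kilograms are the only workable form.* Body mass change with percent-fat change is also full rank (variance inflation factor 1.4 to 2.8).
- *That a singular model will be fitted.* No section says that both proportions, or mass with both components, enter together. The planned collinearity check would expose it.
- *That opposing effects would be reported as no association.* That fits body mass change alone. Percent-fat change would often detect something at low to moderate correlation, and body mass change does better when only fat-free loss matters.

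The reply does not cover the selection rule. That rule is stated, not omitted, and it serves the article's own rationale poorly. An unstated scale alone would not be a finding.

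**Conclusion.** The point holds in limited form. As written, the plan is likely to detect that some composition association exists, but it does not reliably attribute it to fat or to fat-free mass. Under the assumed inputs, the gap between screening and a joint model is small when the two changes are uncorrelated (80% against 84%). It is large at correlations of 0.3 to 0.7 (34% against 82%, falling to 0% against 57%).

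The size depends on the assumed SDs, effects and correlation, none of which the documents supply, and on effects that truly oppose. At very high correlation neither approach does well. Fat-free mass is also not the same as muscle mass, so even the joint model addresses the rationale only approximately. This is a cheap improvement that does not threaten the study's wider aim.

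**What to change.** In Statistics and analysis, before data are examined:

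1. Define the composition exposures as change in fat mass (kg) and change in fat-free mass (kg), visit 2 minus visit 1, computed from recorded mass and proportions.
2. Prespecify one composition model per outcome holding both changes together plus the chosen confounders. Report both coefficients with confidence intervals.
3. Exempt this pair from the rule that keeps only significant measures.
4. Keep body mass change in its own model, and never enter it alongside both components.

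The cost is a few sentences and one extra model term; no new measurement or participant is needed. The downside is some loss of precision if the two changes are highly correlated. At correlation 0.9 the variance inflation factor of about 5.5 means a tolerance of 1/5.5 = 0.18, just under the plan's 0.2 flag. The text should say that such a flag is reported and does not trigger removal of either term.

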Data from the Active Together service shows that many patients are unable to attend assessment appointments prior to surgery, often due to short notice of surgery dates. This might lead to missing data at the presurgery assessment point (visit 2). All efforts will be made to make attending appointments as convenient as possible for patients. Additionally, patients are routinely weighed before surgery; therefore, the key outcomes of body mass change and surgical outcomes should always be available. Therefore, statistical analyses for body mass change will include all participants, and analyses including body composition, size and shape, and questionnaire data will be performed on a smaller cohort if some data are missing.

Complete case analyses will be performed when covariates (eg, body composition variables) contain missing data. Complete case analysis can lead to biased parameter estimates in regression models if the data are not missing completely at random (MCAR). Therefore, graphical techniques and Little’s hypothesis test of the MCAR assumption will be used to explore whether the MCAR assumption is a reasonable one to make with the collected data. If not, a standard multiple imputation method will be implemented (eg, Multiple Imputation by Chained Equations, Linear Regression Imputation or Predictive Mean Matching).

For linear regression analyses, assuming a medium effect size (F^2^=0.15), significance level=0.05, power=0.8 and number of predictors=6, a sample size of 98 is required.^33^ For correlation, assuming a two-tailed test, a medium effect size (rho=0.3), significance level=0.05 and power=0.8, a sample size of 84 is required.^33^ Therefore, a sample size of 100 participants is required to detect medium effect sizes with acceptable statistical power. Furthermore, 100 participants is a reasonable estimate of the number of potential participants within the study’s time frame based on the demographics of current and previous Active Together patients (ie, number of patients awaiting surgery for upper GI or colorectal cancer with a BMI ≥30 kg/m^2^).

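### Both described routes to visit 2 are in person, so its questionnaires are at risk when surgery comes at short notice; the weight-loss intention questionnaire has no listed backup

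*Protocol article*

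**What the plan says.** All references are to the protocol article.

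- **Main route (Procedures, Primary data).** "Participants will be required to attend the Advanced Wellbeing Research Centre (AWRC) at Sheffield Hallam University on two separate occasions". EQ-5D-5L and PG-SGA-SF are completed at visit 1. For visit 2, "the data collection for this visit will be the same as visit one, with the addition of another questionnaire"; the added form covers weight-loss intentions, strategies and advice.
- **Alternative route (same section).** For people who say they cannot get to the centre, "a member of the research team will conduct the two data collection sessions where the participant attends Active Together sessions". These sessions "instead only include body mass and composition measurement performed using the bioelectrical impedance scales and questionnaires".
- **Expected non-attendance (Statistics and analysis).** From the service's own data, "many patients are unable to attend assessment appointments prior to surgery, often due to short notice of surgery dates". The article says that this might leave data missing at visit 2 and that efforts will be made to make appointments convenient.
- **What is protected and what is not (same section).** Because patients are routinely weighed before surgery, "the key outcomes of body mass change and surgical outcomes should always be available". By contrast, "analyses including body composition, size and shape, and questionnaire data will be performed on a smaller cohort if some data are missing".
- **Another source of two of the forms (Table 1 and Figure 1 caption).** Active Together also collects EQ-5D-5L and PG-SGA-SF, at baseline, pretreatment, post-treatment and 90 days. The caption warns that "pretreatment and post-treatment assessments may occur at varying intervals from surgery".

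**The concern.** The missed-visit plan treats the questionnaires like the laboratory measurements. Plethysmography and body scanning need equipment. A questionnaire does not, and the alternative route shows this, since it drops the BOD POD and the scanner and keeps the forms. Yet the article describes no way to obtain the forms from someone who cannot attend before surgery. The alternative route does not fill the gap: it is also in person, and it is meant for people who cannot reach the centre, not for someone whose operation is suddenly brought forward.

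Two things are at stake. Quality of life and nutritional status are outcome domains in the stated aim, and their preoperative values would be missing disproportionately in patients operated on at short notice, so the remaining cohort could be selected as well as smaller. In addition, the weight-loss intention form is given only at visit 2. The planned comparison of intentional loss, unintentional loss and no loss depends on it. A patient who lost weight and missed visit 2 would have a weight change from routine weighing, but could not be placed in the intentional or the unintentional group.

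**Working it through.** **1. What survives a missed visit 2**

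| Item | Source if visit 2 is missed |
|---|---|
| Body mass | Routine weighing before surgery |
| Surgical outcomes | Hospital records |
| Body composition, size and shape | No substitute named |
| EQ-5D-5L, PG-SGA-SF | Active Together pretreatment forms, if completed and if timed near surgery; not named as a substitute |
| Weight-loss intention form | None; not in Table 1 |

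**2. The plan's own sample sizes**

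- Regression, f² = 0.15, 6 predictors, two-sided 0.05, power 0.80: the overall F test with 6 and n − 7 degrees of freedom and noncentrality 0.15n gives n = 98 (power 0.804). This matches the stated 98.
- Correlation, rho = 0.3: n = ((1.960 + 0.842)/atanh 0.3)² + 3 = 84.9, so 85. With the bias term and the exact t critical value, n = 84 gives power 0.7996. The stated 84 is reproduced.
- With 100 recruited, the margin is 2 for regression and 16 for correlation. No allowance for missed visits is stated.

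**3. Effect of missed visits**

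The article says many and gives no rate, so the missed share m is assumed. Questionnaire n = 100(1 − m). Correlation power = Φ(atanh(0.3)·√(n − 3) − 1.960), with atanh(0.3) = 0.3095. For n = 80: 0.3095 × √77 − 1.960 = 0.756, and Φ(0.756) = 0.775.

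| Missed (assumed) | n | Correlation power | Regression power (step 2 F test) |
|---|---|---|---|
| 20% | 80 | 0.78 | 0.695 |
| 30% | 70 | 0.72 | 0.618 |
| 40% | 60 | 0.65 | 0.532 |

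**4. Effect of recovering some forms**

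If a share r of missed forms is obtained remotely, n = 100(1 − m(1 − r)). For example, m = 0.20 and r = 0.70 gives 100(1 − 0.06) = 94. Both shares are assumed. Cells show n and correlation power.

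| Missed | r = 30% | r = 50% | r = 70% |
|---|---|---|---|
| 20% | 86, 0.81 | 90, 0.82 | 94, 0.84 |
| 30% | 79, 0.77 | 85, 0.80 | 91, 0.83 |
| 40% | 72, 0.73 | 80, 0.78 | 88, 0.81 |

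**5. Which analyses these figures cover**

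The recovered n applies where a visit 2 questionnaire is related to body mass change or to surgical outcomes, and to the intention subgroups in terms of numbers classified. An analysis of visit 2 questionnaires against change in fat mass, fat-free mass or body size still needs an attended visit 2, and its n does not change.

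**The case against.** A reader might infer that the questionnaires can be completed only in person, that they will be lost, and that they have no fallback at all. The documents do not support that.

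- **Nothing forbids remote completion.** The article describes in-person routes and is silent on others, and a condensed article may leave such detail to the full protocol. This stands as a limit on the wording. It does not remove the point, because the article does set out what happens when visit 2 is missed, and there it gives a fallback to body mass and accepts a smaller cohort for questionnaires.
- **Loss is possible, not certain.** The article says that visit 2 data might be missing. At-risk is the right term.
- **There is a partial backup.** Active Together collects EQ-5D-5L and PG-SGA-SF at pretreatment. Without neoadjuvant therapy, that assessment should precede surgery. But the attendance warning comes from this same service, the timing varies relative to surgery, and the article does not say these forms replace visit 2. How often the same patient misses both is unknown. The intention form is not covered.
- **Missing data are addressed.** The plan acknowledges complete-case bias, checks whether data are missing completely at random, and turns to multiple imputation if that is not reasonable. This can reduce bias, but it does not supply answers that were never collected.
- **Short notice also limits remote contact.** The team must learn the date and reach the patient before surgery, so recovery will be incomplete. The only cause the article names is short notice; travel is not given there as a reason.
- **The research is exploratory, and body mass change and surgical outcomes are protected.** True, and this limits the weight of the point.

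**Conclusion.** The point holds as a design weakness that can be reduced cheaply, not as an error or a contradiction. Both described routes to visit 2 need attendance, the article itself expects many pre-surgery appointments to be missed, and only body mass and surgical outcomes are given protection. EQ-5D-5L and PG-SGA-SF are at risk with a partial backup. The weight-loss intention form is the most exposed, because it has no listed backup and a planned comparison depends on it.

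The size rests on assumed rates. At 20% to 40% missed, correlation power for rho = 0.3 is 0.78 to 0.65 against a target of 0.80, so at the low end the loss of power is small. Recovering 70% of missed forms would give 0.84 to 0.81; recovering 30% would give 0.81 to 0.73. The stated sample sizes of 98 and 84 are not in question. Analyses that need visit 2 body composition or size gain nothing.

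**What to change.** In Procedures, Primary data, add that a participant who cannot attend visit 2 may complete all visit 2 questionnaires, including the weight-loss intention form, by telephone, post or online, before surgery and within the same 2-week window. In Statistics and analysis, state that these answers are paired with the routine pre-surgery weight, that the mode of completion is recorded, and that the questionnaire analyses are repeated without remote responses as a sensitivity check. State also that analyses using visit 2 body composition or size remain limited to those measured at visit 2.

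The cost is a wording change, any approval that the amendment needs, and a short call, link or mailing by the existing team for each missed visit. The downside is a small possible difference by mode of completion, which the recorded mode and the sensitivity check make visible. The change is worth making before recruitment has progressed far, because preoperative answers cannot be collected after surgery.
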